## Abstract

**Background:**

Lack of physical activity is an important risk factor for overweight, diabetes, cardiovascular disease and other chronic conditions. In the Netherlands, ethnic minority groups are generally less physically active and rate their own health poorer compared to ethnic Dutch. This applies in particular to women. For this reason women from ethnic minority groups are an important target group for interventions to promote physical activity.

In the Netherlands, an exercise referral program ("Exercise on Prescription") seems successful in reaching women from ethnic minority groups, in particular because of referral by the general practitioner and because the program fits well with the needs of these women. However, the effect of the intervention on the level of physical activity and related health outcomes has not been formally evaluated within this population. This paper describes the study design for the evaluation of the effect of "Exercise on Prescription" on level of physical activity and related health outcomes.

**Methods:**

The randomized controlled trial will include 360 inactive women from ethnic minority groups, with the majority having a non-Western background, aged between 18 and 65 years old, with regular visits to their general practitioner. Participants will be recruited at healthcare centres within a deprived neighbourhood in the city of The Hague, the Netherlands.

An intervention group of 180 women will participate in an exercise program with weekly exercise sessions during 20 weeks. The control group (n = 180) will be offered care as usual. Measurements will take place at baseline, and after 6 and 12 months. Main outcome measure is minutes of self reported physical activity per week. Secondary outcomes are the mediating motivational factors regarding physical activity, subjective and objective health outcomes (including wellbeing, perceived health, fitness and body size) and use of (primary) health care. Attendance and attrition during the program will be determined.

**Conclusion:**

This trial will provide information on the effectiveness of an exercise referral scheme on the short and long term among women from ethnic minority groups, mainly non-Western, in the Netherlands. The results of this study will contribute to the evidence base for interventions in ethnic minority populations.

**Trial registration:**

Dutch Trial register: NTR1294

## Background

Regular physical activity plays an important role in the prevention and treatment of overweight, diabetes, cardiovascular disease and other chronic conditions [1-5]. In the Netherlands, only half of the population meets the current recommendations for physical activity [1]. Several studies have shown that ethnic minority populations in the Netherlands are even less physically active than the ethnic Dutch population [1,6]. This lack of physical activity may be one of the factors explaining disparities in health. For example, Turkish and Moroccan women are more often overweight (respectively 72% and 64%) than ethnic Dutch women (45%) [1]. In addition, Turkish, Moroccan and Surinamese women more often suffer from diabetes mellitus, hypertension, and mental health problems than Dutch women in the same age group and rate their own health poorer [7-10].

For this reason women from ethnic minority groups are an important target group for interventions to promote physical activity. Of the interventions that have been developed in the Netherlands over the past years, "Exercise on Prescription" is one that seems successful in reaching ethnic minority populations [11,12]. Interventions such as "Exercise on Prescription" are internationally referred to as exercise referral schemes (ERS) [13,14]. In ERS, patients who are physically inactive or have related health problems are referred by their general practitioner to supervised exercise activities. Trained instructors collaborate with the general practitioners to support the ongoing rehabilitation of those referred. There have been several studies that evaluated the effect of ERS among the general population [13,15-18]. These studies generally indicated that ERS have a small but positive effect on increasing physical activity in sedentary people. However, to date no study has examined the effect of ERS in promoting physical activity on participants from varying ethnic minority groups.

A process evaluation of the Dutch program "Exercise on Prescription" (EoP) showed that it successfully reaches women from ethnic minority groups, mostly with a Surinamese, Turkish and Moroccan background [19]. Qualitative interviews among participants showed that EoP is attractive for these women because of the facilitating role of the health professional, the supportive environment, a financial incentive (in the form of a discount after successful completion of the program), supervision by fitness instructors, the proximity of locations and the possibility of 'women-only' exercise groups [19]. Women also indicated in the interviews that they had become more physically active and that their (subjective) health and psychosocial well- being had improved. Moreover, 74% said that they intended to keep exercising after participation in EoP ended [11]. While these experiences with EoP seem very positive, the effect of the intervention on the level of physical activity, related health (problems) and use of health care has not been formally evaluated. The ongoing program of EoP in the city of The Hague, The Netherlands offers an interesting opportunity to study these effects among ethnic minority groups.

Therefore the objective of our study is to evaluate the effect of EoP on physical activity among women with mainly a non-Western ethnic background. Based on social cognitive models, the assumption is that this exercise intervention will finally result in a behaviour change via a positive influence on the intention and attitudes towards physical activity [20]. Therefore, we will also evaluate the effects on the intention and motivational factors with regard to physical activity (attitudes, social influence and self-efficacy). It is expected that increased physical activity will positively affect objective health (fitness, body size), subjective health (perceived health and well-being) and use of health care. Therefore also these outcome measures will be assessed additionally to the level of physical activity. Finally, attendance and attrition during the program will be determined.

## Methods

### Objectives

The present study aims at evaluating the effect of EoP, an exercise referral scheme, on the level of physical activity of women from ethnic minority groups in the Netherlands. In addition, the effect of this intervention on mediating motivational factors, health and use of health care will be evaluated. The study addresses the following questions:

1) What is the effect of participation in EoP on the level of physical activity as measured by self-reported physical activity (both immediately after the programme and six months after completion of the programme)?

2) What is the effect of participation in EoP on the intention and motivational factors with regard to physical activity (e.g. attitudes, social influences and self-efficacy)?

3) What is the effect of participation in EoP on the subjective health status of participants (perceived health and well-being) and objective elements of health (fitness of the participants and body size)?

4) What is the effect of participation in EoP on the use of (primary) health care?

Furthermore, the participation and the follow-up rate in the study (and differences between relevant sub-groups) will be assessed as well as the reasons for non-participation or loss to follow-up.

### Study Design

The study will be set up as a randomized controlled trial comparing referral to an exercise program (Exercise on Prescription (EoP)) and usual care. To evaluate the effect of the intervention it is important that we follow the referral procedure as it is currently carried out by the general practitioners. Therefore, in this study we will use pre-randomisation, which refers to a procedure in which participants are randomly allocated to the control or the intervention group without first obtaining informed consent. Whenever a women allocated to the intervention group visits her GP, she will be referred to EoP if she meets the criteria (ethnic minority background, aged 18–65 years, physically inactive). The women will be asked for informed consent after the referral. If the patient is allocated to the control group the GP will not refer the patient to EoP but provide care as usual which includes lifestyle advices regarding physical activity when necessary. This implies that the control group is not informed about the intervention or the purpose of the study as this knowledge may lead to attrition of controls, because they may prefer participating in the exercise intervention and therefore not participate in the study. As a result the control group would not be a random selection and this may lead to less valid study results. This procedure of pre-randomisation is commonly accepted in situations where knowledge of the intervention (and the study's aim) can influence the study results [21].

### Randomisation

We will use a concealed procedure for randomisation of women using a computer generated randomisation list developed by an independent person.

### Ethical Considerations

This study is approved by the Medical Ethics Committee of Academic Medical Centre of Amsterdam, and is registered within the Dutch Trial Register (NTR1294).

Participants in the intervention group also receive a letter from their GP in which they are invited to visit their GP to discuss participation in EoP. Participants who are referred to EoP will be informed about the study and asked for their participation following the intake at EoP. They will receive similar information on the purpose of the study as the control participants. In this way we hope to avoid bias in the results as a consequence of social desirable answers (or behaviour) due to the fact that people are aware of the study's purpose. All written material such as letters and leaflets will be available in Dutch and Turkish. Given the demographics of the concerning deprived neighbourhoods in The Hague it is expected that the largest group within our study population will have a Surinamese, Turkish or Moroccan background. The main language used among Moroccan people in the Netherlands is Berber, but this is not a written language. Therefore, we could not translate the materials for Moroccan women. Surinamese people generally speak the Dutch language fluently.

### Intervention

The general practitioner will offer participation in Exercise on Prescription (EoP) to every eligible woman in the intervention group. EoP programme is financed by the municipality of The Hague and several health insurance companies. The programme is set up to promote physical activity among inhabitants of deprived neighbourhoods in The Hague by letting them experience the beneficial effects of sports and to stimulate them in such a way that they are able to continue the behaviour after completion of the programme. The main focus of the programme is on increasing participation, empowerment of the client, providing tailored activities, and increasing motivation through personal coaching. All these factors have been shown to be important parameters of behavioural changes [23].

#### Intake

Over the past years a protocol for EoP has been developed and tested in practice. This protocol consists of an intake followed by 20 sessions of supervised physical activity and a final evaluation. During the intake, the lifestyle advisor will document the individual goals and preferences with regard to physical activity and organise the participation in the exercise activities.

#### Supervised activities

After the intake, participants will be contacted again when the next available exercise course starts. At the start of the course, participants pay a contribution of 50 euros. Of these 50 euros 10 will be returned after successful completion of the programme, i.e. at least 85% attendance. Attendance is monitored by the lifestyle advisors, who are instructed to immediately contact a participant whenever she misses a session. This is considered an important part of the motivation strategy and will therefore also be part of the strategy employed in the study. At present, EoP offers Fitness, Aquarobics, Aerobics and Dancing [24]. In order to promote participation, all important issues that became evident in an earlier process evaluation of EoP will be taken into account [11]. For example, as part of the programme both daytime and evening group exercise sessions will be offered in groups accessible to women only. The timing will be such that the courses do not coincide with school times. Moreover, the courses will be organised at several locations throughout the city that are easily accessible by public transport, with a focus on those neighbourhoods with large ethnic minority populations. The physical activity component of the program is aimed at increasing cardiovascular fitness and muscle power.

The personal coaching during EoP is organised in two parts. The first ten supervised sessions are aimed at motivating the participant through increasing awareness of the positive effects of exercise. The following ten sessions are dedicated to empowering the participant with respect to the continuation of the healthy (physical) behaviour. During the sessions the participants are given individual advice as to how to reach the goal of exercising 30 minutes a day for at least 5 days a week, either by increasing daily physical activity (walking etc.) or by further participating in (un)organised sports. In addition, experienced social support, attitudes towards sports and ways of coping with (negative) feedback from community will be addressed. This supervision and coaching is done by specially trained sports instructors, under the responsibility of the lifestyle advisor.

#### Final evaluation with lifestyle advisor and further referral

After the first 20 weeks, a final evaluation takes place with the lifestyle advisor in which the individual's achievements, further goals and experiences in the programme are evaluated. At the same time, the lifestyle advisor will refer the participants to "Exercise without Prescription" [25]. Exercise without Prescription was designed to address a further aspect that was deemed important by participants in the process evaluation of EoP, namely that participants experienced difficulty in continuing the desired behaviour after EoP. In Exercise without Prescription participants are guided further through the transition of supervised activity to independent activity, through a motivational counselling session in which the participant is stimulated to continue and actively plan healthy behaviour. This is supplemented with regular invitations for free try-out lessons activities at local clubs, fitness centres or community centres. Moreover, an important part of the Exercise without Prescription programme is the possibility of a discounted membership at a fitness centre and several local facilities.

### Control Group

Women in the control group will receive care as usual and will only be approached by a professional interviewer for an interview on lifestyle (in their preferred language if possible) and measurements. Participating women will receive a voucher of 10 euro to stimulate participation in the study (participants in the intervention group will receive this voucher as well).

### Outcome Measures

The primary outcome measure is self-reported physical activity measured in minutes per week. Secondary outcome measures are a) the intention and motivational factors with regard to physical activity (e.g. attitudes, social influences and self-efficacy) b) subjective health outcomes (perceived health and well-being) c) objective health outcomes: fitness of the participants (oxygen uptake) and body size (body mass index, waist-hip ratio and waist circumference, and fat percentage) d) the use of (primary) health care. Furthermore, the participation and the follow-up rate in the study will be assessed as well as the reasons for non-participation or loss to follow-up. Baseline demographic characteristics, such as age, ethnicity, neighbourhood of residence and other socioeconomic factors of potential participants will be recorded.

Attendance during the intake, participation in the weekly sports sessions, and the final evaluation (intervention arm) will be monitored by the lifestyle advisor, who will also notify women prior to the appointment and follow-up with women who have not shown up for a session. In addition, data on the individually tailored content of the intervention and subsequent participation in "Exercise without Prescription" will be registered.

### Data Collection

Data collection will take place at baseline (T0, directly following the EoP -intake), after 6 months (T1 shortly after completion of EoP) and after 12 months (T2, follow-up measurement 6 months after completion of EoP) for both the intervention group and the control group (see Figure 1). All interviews and physical examinations will take place in one of the nearby health care centres that participate in the study or, when possible, in case of intervention women at the same location as the meetings with lifestyle advisor.

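### Baseline in the intervention arm follows the EoP intake, and only that arm may be assessed at the lifestyle advisor's location: an avoidable between-arm difference in how T0 is measured

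*Protocol article*

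**What the plan says.** All references are to the protocol article.

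- **Timing of T0.** Data Collection: "Data collection will take place at baseline (T0, directly following the EoP -intake". The sentence goes on to cover both arms, although only one arm has an intake.
- **Status of the intake.** Intake: "This protocol consists of an intake followed by 20 sessions of supervised physical activity and a final evaluation". During it, "the lifestyle advisor will document the individual goals and preferences with regard to physical activity", and the woman's exercise activities are arranged.
- **When intervention women join the study.** Participants and Recruitment: "Participants who are referred to EoP will be informed about the study and asked for their participation following the intake at EoP". Study Design places the consent request after the GP's referral, without mentioning the intake.
- **Contact with controls before T0.** After a GP letter about a health and lifestyle study, a control woman "will only be approached by a professional interviewer for an interview on lifestyle" (Control Group).
- **Place of assessment.** Data Collection makes the participating health care centres the rule, with one exception: "when possible, in case of intervention women at the same location as the meetings with lifestyle advisor".
- **Use of T0.** Data Analyses compares the arms on change in physical activity from T0 to T1 and from T0 to T2. Outcome Measures makes self-reported minutes per week the primary outcome.

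**The concern.** At T0 the two arms answer the same questions from different positions. An intervention woman has just discussed her activity goals with a lifestyle advisor and had her exercise course organised; a control woman has not. The questions cover intention, attitudes, social influence, self-efficacy and minutes of activity. The first four are what a goal-setting conversation could move at once, and the Background treats them as the route by which the programme works. If T0 already contains part of that response, the change from T0 no longer measures the whole of it.

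The site exception adds a second difference. The authors give both arms similar information on the study's purpose, and state why: "In this way we hope to avoid bias in the results as a consequence of social desirable answers (or behaviour". Interviewing one arm at the place where it meets the programme's advisor works against that aim. It can also show the interviewer which arm the woman is in. The Interview section tries to keep the same interviewer for all three visits, so knowledge gained at T0 would carry forward to T1 and T2.

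**Working it through.** The plan gives no figure for this point, so the check is on the structure of the contrast.

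**1. Order of events before T0**

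| | Intervention | Control |
|---|---|---|
| GP | invited to visit, EoP discussed, referred | letter asking permission for contact |
| EoP intake | yes | none |
| Study invitation and T0 | after the intake | interviewer contact only |
| Site | health centre or lifestyle advisor's location | health centre |
| First exercise session | later, when the next course starts (Supervised activities) | none |

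T0 therefore comes after an intervention component in one arm only, but apparently before any supervised exercise.

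**2. How a T0 shift enters the estimate**

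Let Δ be the true effect at T1. Let b be the average shift in an intervention woman's T0 answer caused by the intake. Let s0 and s1 be the average effects of the programme site on answers at T0 and T1 in that arm. The expected difference in change is

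(Δ + s1) − (b + s0) = Δ − b + (s1 − s0).

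- The intake shift b stays in the contrast if it affects T0 and not T1.
- The site effect cancels when s1 = s0. The site exception covers all interviews and examinations, so T0 as well as T1 and T2. Only a change between visits in site use, or in its effect, remains.
- Adjusting for T0 with slope β turns −b into −βb. That is smaller when β lies between 0 and 1, but it is not zero. A T0 difference caused by the intake would also look like chance imbalance in the plan's check of baseline comparability.

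**3. Scale for the primary outcome, under assumed values of b**

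The Sample Size Calculation gives a mean of 1852 min/week and a 15% difference: 0.15 × 1852 = 277.8 min/week. No value of b is given, so the values below are assumptions in both directions, with s1 = s0.

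| Assumed b (min/week) | Share of 277.8 | Apparent effect if b is upward | Apparent effect if b is downward |
|---|---|---|---|
| 25 | 9% | 252.8 | 302.8 |
| 50 | 18% | 227.8 | 327.8 |
| 100 | 36% | 177.8 | 377.8 |

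The table shows how a shift would pass through, not how large it is.

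**4. Which outcomes are exposed**

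- Intention, attitudes, social influence and self-efficacy: directly, since they can change during one conversation.
- Self-reported activity: possibly, through reporting. T0 directly follows the intake, so the intake leaves no time for activity itself to change.
- Body size and oxygen uptake: hardly, since exercise has not begun.

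**The case against.** The strongest reply is that little of the intervention has been delivered by T0. Supervised activities places the coaching inside the exercise sessions, and these start later. The Intake section describes only recording goals and preferences and arranging participation. This stands. A reader might infer that T0 is no baseline at all, but the text supports only that it follows referral and goal-setting, which matters mainly for the motivational outcomes.

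Second, a reader might infer that the programme site inflates reported minutes at follow-up while the intake biases T0 the other way. The documents do not support this. The site exception covers every visit, so a constant effect cancels, and no direction is given for either influence. A woman just referred for inactivity might under-report at T0, which would inflate the effect; one who has just set goals might over-report.

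Third, it is tempting to ask for T0 before the GP invitation. That conflicts with Study Design, which adopts pre-randomisation to keep the usual referral route and seeks consent after referral. It would also mean interviewing women later found ineligible or never referred. This objection stands against so early a T0, but not against a T0 between referral and intake.

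Fourth, the protocol does not claim masked interviewers, and women approached through EoP may link the interview to it wherever it is held. A common site would reduce this difference without removing it. The objection stands against any claim that masking is defeated by the site alone.

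Finally, the missing Figure 1 may state when T0 falls for controls.

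**Conclusion.** The point holds as a cheap improvement. T0 follows the programme's first component in one arm only, and one arm alone may be seen at the lifestyle advisor's location. Since effects are changes from T0, this can bias the change in intention, attitudes, social influence and self-efficacy, and possibly in self-reported activity. It is a weak concern for body size and fitness.

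The size and direction cannot be derived from the documents. The conclusion assumes only that a goal-setting conversation can alter answers given directly afterwards. The documents do not support a claim that the primary result is biased by a known amount, or that the trial is invalid on this ground. The protocol's case for pre-randomisation explains why women are referred in the usual way and controls are not told of EoP. It gives no reason for the separate site, and it does not require T0 to wait until after the intake.

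**What to change.** 1. In Data Collection, delete the clause that allows assessment "in case of intervention women at the same location as the meetings with lifestyle advisor". Hold all T0, T1 and T2 interviews and examinations in the participating health care centres for both arms.
2. Do not tell interviewers the allocation, accepting that some women will reveal it.
3. Obtain consent and do the T0 interview after GP referral but immediately before the EoP intake. This fits the consent timing in Study Design. The sentence in Participants and Recruitment that places the request after the intake would need to change with it.
4. State the corresponding T0 point for controls, who have no intake to anchor it.

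The cost is a protocol amendment, some rescheduling and some lost convenience for intervention women. A few T0 interviews would be of referred women who then do not attend the intake; they would stay in the intention-to-treat analysis. The change does not remove the influence of the GP's conversation about EoP, which still precedes T0 in one arm only. That remaining difference comes with consent after referral and should be acknowledged when the motivational outcomes are interpreted.
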